## Abstract

**Background:**

Despite the high cardiovascular risk, evidence of efficacy of preventive strategies in individuals with diabetes is scant. In particular, recommendations on the use of aspirin in patients with diabetes mostly reflect an extrapolation from data deriving from other high risk populations. Furthermore, the putative additive effects of aspirin and statins in diabetes remain to be investigated. This aspect is of particular interest in the light of the existing debate regarding the need of multiple interventions to reduce total cardiovascular risk, which has also led to the proposal of a polypill. Aim of the study is to evaluate the efficacy of aspirin in the primary prevention of major cardiovascular events in diabetic patients candidate for treatment with statins. These preventive strategies will be evaluated on the top of the other strategies aimed at optimizing the care of diabetic patients in terms of metabolic control and control of the other cardiovascular risk factors.

**Methods/Design:**

The ACCEPT-D is an open-label trial assessing whether 100 mg/daily of aspirin prevent cardiovascular events in patients without clinically manifest vascular disease and treated with simvastatin (starting dose 20 mg/die). Eligible patients will be randomly assigned to receive aspirin + simvastatin or simvastatin alone. Eligibility criteria: male and female individuals aged >=50 years with diagnosis of type 1 or type 2 diabetes, already on treatment with statins or candidate to start the treatment (LDL-cholesterol >=100 mg/dL persisting after 3 months of dietary advise). The primary combined end-point will include cardiovascular death, non-fatal myocardial infarction, non-fatal stroke, and hospital admission for cardiovascular causes (acute coronary syndrome, transient ischemic attack, not planned revascularization procedures, peripheral vascular disease). A total of 515 first events are needed to detect a reduction in the risk of major cardiovascular events of 25% (alpha = 0.05; 1-beta = 0.90). Overall, 5170 patients will be enrolled. The study will be conducted by diabetes specialists and general practitioners.

**Discussion:**

The study will provide important information regarding the preventive role of aspirin in diabetes when used on the top of the other strategies aimed to control cardiovascular risk factors.

**Trial registration:**

Current Controlled Trials ISRCTN48110081.

## Background

Macrovascular complications represent the leading cause of morbidity, mortality, and resource consumption in type 2 diabetes, and their burden is expected to grow in the next years due to the increasing incidence of the disease worldwide.

Individuals with type 2 diabetes have a two- to fourfold increased risk of cardiovascular disease (CVD) compared with non-diabetic subjects and CVD mortality rates are 1.5–4.5 times higher than in the general population [1]. The increase in the incidence of coronary events is greater for more severe clinical outcomes, such as myocardial infarction and sudden death, than for less serious outcomes, such as angina pectoris [1]. Furthermore, the case fatality rate after a myocardial infarction among individuals with diabetes is higher than that for patients without diabetes; after a first cardiac event, 50% of patients with diabetes die within one year, and half of those who die do so before they reach the hospital (sudden deaths) [2]. The high incidence of sudden deaths makes primary prevention particularly relevant in this population. In addition, it has been shown that diabetic patients without previous myocardial infarction have as high a risk of myocardial infarction as non-diabetic patients with previous myocardial infarction [3]. These findings make the differentiation between primary and secondary prevention in individuals with diabetes almost irrelevant and suggest the need for treating cardiovascular risk factors aggressively.

Despite the very high cardiovascular risk profile, evidence of efficacy of preventive strategies in individuals with diabetes is surprisingly scant. In particular, the existing recommendations [4] regarding the use of aspirin and statins for the prevention of cardiovascular events in patients with diabetes reflect more an extrapolation from data deriving from other high risk populations, rather than reliable evidence based on studies specifically designed for individuals with diabetes. The substantial lack of clear evidence is reflected by the low use of this drug in clinical practice; in fact, only 10% of diabetic patients are treated with aspirin for the prevention of cardiovascular events [5].

While the efficacy of aspirin versus placebo in patients with diabetes is currently under investigation, the putative additive effects of aspirin and statins in this population remain to be investigated. This aspect is of particular interest in the light of the existing debate regarding the need of multiple interventions to reduce total cardiovascular risk, which has also led to the proposal of a polypill [6]. To this respect, a recent nested case-control study suggests that the greater benefit in terms of mortality reduction in patients with ischemic heart disease is achieved when the multiple drug intervention included statins, aspirin and β-blockers and/or ACE-inhibitors [7]. Nevertheless, no specific information is available for patients with diabetes mellitus, for whom there is the suspicion that aspirin could be less effective [8], making additional research urgently needed.

This situation is particularly worrisome when considering that a tight metabolic control, while representing a cornerstone of diabetes care, is not per se sufficient to substantially decrease the cardiovascular risk. On the other hand, there is a substantial lack of reliable information about the benefits of primary prevention strategies aimed at reducing the overall risk associated with diabetes. For all these reasons, the evaluation of cardiovascular preventive strategies in patients with diabetes represents a priority in terms of public health.

### Rationale to test the efficacy of aspirin for the prevention of cardiovascular events in diabetes mellitus

Data on primary prevention of cardiovascular events in individuals with diabetes and no evidence of cardiovascular disease are scarce. The meta-analysis on the efficacy of antiplatelet therapy showed a clear benefit for the whole population of over 140.000 subjects (22% reduction in the risk of major cardiovascular [CV] events), but no statistically significant benefit was documented in the subgroup of about 5.000 diabetic patients (7% risk reduction) [9]. More recently, an analysis on more than 1000 patients with diabetes enrolled in the Primary Prevention Project (PPP) confirmed a non statistically significant reduction of 10% in the incidence of major CV events in individuals treated with aspirin as compared with controls [10].

Another puzzling result regarding the efficacy of aspirin in primary prevention comes from the recent data of Womens' Health Study [11] suggesting biological differences between men in women in their response to aspirin. This study showed that aspirin had no significant effect on the risk of myocardial infarction or cardiovascular death neither in women without diabetes, nor in those with diabetes.

The lack of adequate statistical power can represent the more obvious explanation for the failure in documenting a clear benefit of antiplatelet therapy in the primary prevention of cardiovascular events in subjects with diabetes.

On the other hand, diabetes could represent a special case of aspirin resistance [8], although no specific studies have, to our knowledge, fully explored this hypothesis. The reason for the apparently reduced aspirin efficacy in diabetic patients remains largely unclear, however both, intraplatelet mechanisms and extra-platelet inflammatory-thrombogenic factors may contribute to the complexity of aspirin failure in diabetic patients.

In high risk patients treated with aspirin, inadequate suppression of Cox-1 as documented by high levels of serum thromboxane-2 [12] or urinary thromboxane metabolites [13], may be associated with increased risk of recurrent cardiovascular events.

Moreover, in some cases the antiplatelet effects of aspirin can be overwhelmed by aspirin-insensitive mechanisms of platelet activation and thrombus formation, mainly related to an up-regulated vascular inflammatory reaction [8,14].

From this point of view, several studies have documented that diabetes is associated with elevated levels of C-reactive protein [15] and endothelial adhesion molecules, considered as markers of the endothelial inflammatory response [16,17]. Diabetes is also associated with a reduction in the production of, and sensitivity to nitric oxide and PGI2, two of the most important antiaggregants. Furthermore, an increased platelet sensitivity to aggregant agents has also been described [18].

### Rationale for association of aspirin and statins

It has been recently shown that platelet response to aspirin is linearly reduced with increasing cholesterol plasma levels. The presence of dyslipidemia, particularly common among diabetic patients, could thus be at least partially responsible for a lower efficacy of aspirin in this population [19]. The concomitant use of statins could thus restore the normal platelet sensitivity to aspirin by reducing cholesterol levels.

One additional reason to hypothesize a positive effect of statins in improving platelet response to aspirin is related to their anti-inflammatory properties. Several studies have shown that treatment with statins is associated with a decrease in the levels of C-reactive protein in just a few weeks [20,21]. Statins also decrease the activity of inflammatory cells [22]. Clinical and experimental studies have shown that statins can reduce endothelial dysfunction by increasing the production of nitric oxide (NO), decreasing the synthesis of endothelin-1 and inhibiting the LDL cholesterol oxidation [23]. This class of drugs has also been shown to increase atherosclerotic plaque stability by reducing macrophage cholesterol accumulation and production of metalloproteases [23]. Therefore, if an upregulated vascular inflammatory reaction is responsible for aspirin resistance, it is plausible to hypothesize that statins would also improve the clinical response to aspirin therapy.

On the other hand, if platelets of diabetic patients were normally inhibited by aspirin, but other thrombogenic stimuli not inhibited by aspirin overwhelm aspirin action, statins could exert a complementary action by inhibiting these mechanisms; in fact, statins may exert antithrombotic effects by interfering with platelet adhesion and aggregation, expression of tissue factor and plasminogen activator inhibitor-1 (PAI-1), fibrinogen concentration and blood viscosity [22].

Given these premises, it is of crucial importance to conduct a large-scale, pragmatic trial to evaluate the effectiveness of aspirin use in primary prevention of cardiovascular events in association with statins therapy when included in a strategy of global risk control.

The choice of simvastatin is based on economical considerations; in fact, Simvastatin is the only statin available in Italy as an equivalent product, thus implying substantially lower costs in comparison with brand products.

If the combination of aspirin and simvastatin will prove to be effective in reducing diabetes morbidity and mortality, this will also translate into a dramatic decrease in the costs for the Italian health care system.

## Methods

### General objective

Aim of this trial is to evaluate the efficacy of low-dose aspirin (100 mg/daily) in the prevention of major cardiovascular events in diabetic patients without clinically manifest vascular disease and candidate for treatment with statins. These preventive strategies will be evaluated on the top of the other strategies (including lifestyle interventions and pharmacological treatments) aimed at optimizing the care of diabetic patients in terms of metabolic control and control of the other cardiovascular risk factors (obesity, hypertension, and smoking).

#### Primary objectives

To assess the effects of low dose aspirin on the incidence of major vascular events (defined as a combined end-point of cardiovascular death, non-fatal myocardial infarction, non-fatal stroke, or inpatient or outpatient hospital admission for cardiovascular causes, including acute coronary syndrome, not planned revascularization procedures, peripheral vascular disease), in a wide range of people with type 1 or type 2 diabetes with no clinical evidence of vascular disease and receiving statins treatment.

#### Secondary objectives

Additional aspects to be considered will include total and cause specific mortality, venous thromboembolic episodes, major hemorrhagic episodes, and total number of hospitalizations for cardiovascular causes (myocardial infarction, stroke, acute coronary syndrome, not planned revascularization procedures, heart failure, transient ischemic attack, peripheral vascular disease, lower limb revascularization procedures).

The study will also describe the natural history of the disease under routine clinical practice conditions, particularly with reference to the degree of control of the other cardiovascular risk factors.

The coherence in the effects of low dose aspirin across different patients subgroups defined according to their baseline characteristics/risk (i.e. gender, age, type of diabetes, metabolic control, baseline cholesterol levels, presence of microvascular complications, treatment with other cardiovascular drugs) will also be assessed.

### Study design

This is a trial designed to assess whether 100 mg/daily of aspirin prevent cardiovascular events in diabetic patients without clinically manifest vascular disease and treated with simvastatin (starting dose 20 mg/die).

A prospective, randomized, open, blinded endpoint evaluation (PROBE) design will be adopted [24].

Eligible patients will be randomly assigned (ratio 1:1) to receive aspirin + simvastatin or simvastatin alone (Figure 1).

**Figure 1 F1:**
[figure not shown]
Study design.

### Study population

Male and female subjects aged ≥50 years are eligible for the study if they meet the following inclusion criteria:

#### Inclusion criteria

• Written informed consent to participate in this study;

• Clinical diagnosis of type 1 or type 2 diabetes, based on standard diagnostic criteria (Patients on treatment with oral hypoglycaemic agents or insulin or with fasting plasma glucose ≥126 mg/dl, confirmed on a second occasion, or 2 hour post-challenge glucose (after 75 g OGTT) ≥200 mg/dl) irrespective of diabetes treatment;

• Need for statin treatment:

◦ Patients already receiving statin therapy irrespective of their actual LDL cholesterol and total cholesterol levels or

◦ Patients not currently on statin treatment with LDL-cholesterol levels ≥100 mg/dL (2.59 mmol/L) persisting after three months of dietary advise (Threshold levels for the initiation of statin treatment according to Third Joint Task Force of European and other Societies on Cardiovascular Disease Prevention in Clinical Practice [25]);

• Ability and willingness to comply with all study requirements.

#### Exclusion criteria

• Previous major vascular events (non-fatal myocardial infarction, non-fatal stroke, angina, transient ischemic attack, revascularization procedures, peripheral vascular disease);

• Poor metabolic control (HbA_1c _> 14.0%);

• Any condition requiring elective treatment with aspirin;

• Contraindications to aspirin (history of aspirin allergy, bleeding tendency, gastrointestinal haemorrhage or peptic ulcer within six months, active hepatic disease, asthma, renal failure, use of anticoagulant therapy.

• Contraindications to simvastatin (history of allergy, chronic liver disease or abnormal liver function [i.e. ALT or AST ≥1.5 times the upper limit of normal], severe renal disease or evidence of renal impairment [i.e. creatinine >2 mg/dl], concomitant use of potent inhibitor of CYP3A4.

• Chronic use of non-steroidal anti-inflammatory drugs;

• Presence of any life-threatening condition;

• Child-bearing potential (pre-menopausal women not using reliable contraception);

• History of active substance or alcohol abuse within the last year.

### Participating centres

The study will be conducted by diabetes specialists and general practitioners with a long experience of participation in clinical trials.

### Study treatments

All randomized patients will be instructed to take one or two tablets daily; in particular, if the patient will be assigned to "aspirin+simvastatin arm", he will be instructed to take one tablet containing simvastatin (one 20 mg tablet every evening), and the other containing aspirin. Otherwise, the patient will be instructed to take one tablet containing simvastatin.

Study drugs will be prescribed by the investigator.

An initial dose of 20 mg/daily of simvastatin will be prescribed to patients not previously on treatment with statins.

The dose of simvastatin can be increased to 40 mg/day at month 3 in those patients whose plasma LDL cholesterol remains ≥100 mg/dL (2.59 mmol/L).

Patients already on statins treatment at study entry will be shifted to the equivalent dose of simvastatin without the need for a drug-free period.

Changes in simvastatin doses are allowed throughout the study based on clinical judgment.

If target LDL cholesterol levels will not be reached with 40 mg/daily, clinicians may modify therapeutic strategies (changes of statin, addition of other drugs such as ezetimibe, fenofibrate, nicotinic acid, omega-3 fatty acid).

Treatment will be centrally assigned on telephone, after verification of the correctness of inclusion and exclusion criteria. A separate computer-generated randomization table will be produced for each physician/diabetes centre in random permuted blocks. Each randomized patient will receive a unique subject identification number.

### Sample size estimates

The sample size calculation is based on the cardiovascular event rate occurred in over 1000 diabetic patients without evidence of cardiovascular disease enrolled in the PPP trial [10]. This study was conducted with the participation of both General Practitioners and Diabetes Clinics in Italy, thus closely reflecting the setting of care and the context in which the ACCEPT-D trial will be conducted. In the PPP trial the cumulative incidence of major cardiovascular events (cardiovascular death, myocardial infarction, stroke, transient ischemic attack, peripheral vascular disease, revascularization procedures), after a median follow-up of 4 years, was of 11.5% in subjects not assigned to aspirin treatment (incidence rate of 2.88% per annum). Assuming that treatment with statins can reduce such an event rate by approximately one quarter (based on the results of the meta-analysis of primary prevention studies in patients with diabetes [26]), we can expect an incidence rate of major cardiovascular events of about 2.1–2.2% per annum. Since the primary cumulative end-point of the study also includes hospitalizations for major vascular causes, sample size calculations for the proposed trial are based on a conservative estimated 2.5% annual rate of major vascular events.

Aspirin has been shown to reduce major cardiovascular events by about one quarter in a wide range of high risk populations [27,28]. The sample size is thus estimated to detect with a statistical power of 90% (α = 0.05) a reduction in the risk of major cardiovascular events of 25% (HR = 0.75).

Given these assumptions, a total of 515 first events are needed for the primary efficacy analysis. Therefore, the total number of subjects to be enrolled is of 4.700 patients, to be followed up for five years. From the PPP trial [29], it is possible to foresee a trial discontinuation rate of 10%. Therefore, a total of 5.170 patients will be enrolled (2.585 in each treatment arm). A total of 515 events will also ensure an adequate statistical power (i.e. 80%) to detect a smaller reduction in the risk of major events (i.e. HR = 0.78).

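### The 10% discontinuation allowance is added instead of divided out, and 4,700 rests on five-year risk taken as five times the annual rate; expected events and time to 515 should be restated

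*Protocol article*

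**What the plan says.** All figures are in the protocol article.

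- **Sample size estimates** sets "statistical power of 90% (α = 0.05)" for "a reduction in the risk of major cardiovascular events of 25% (HR = 0.75)". It concludes that "a total of 515 first events are needed for the primary efficacy analysis". The event rate is "a conservative estimated 2.5% annual rate of major vascular events".
- From these it states that "the total number of subjects to be enrolled is of 4.700 patients, to be followed up for five years". It then foresees 10% discontinuation and arrives at "a total of 5.170 patients will be enrolled (2.585 in each treatment arm)". The full stop is a thousands separator. The abstract repeats the total: "Overall, 5170 patients will be enrolled".
- Neither the formula for five-year risk nor the formula for the discontinuation allowance is written out.
- **Study design** gives allocation: "randomly assigned (ratio 1:1)".
- **Timing** makes the trial event-driven with a target of 515. It anticipates five years counted from the first randomised patient, provided that 5,170 are recruited and the rate is 2.5% per year. Enrolment takes 18 months. Follow-up is to be extended if enrolment or the event rate falls short.

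**The concern.** Two steps between 515 events and 5,170 patients looked doubtful.

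First, if 4,700 patients must remain after 10% are lost, the number enrolled is 4,700/0.90. Multiplying by 1.10 gives too few.

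Second, the endpoint is a first event, so patients leave the risk set when they have one. A constant annual rate multiplied by five years then overstates the five-year risk, and so overstates the events that a given number of patients will produce.

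What is at stake is the forecast. The Timing section tells readers that five years suffices if recruitment and event rate are on target, and foresees extension only if one of them is not. The interim analysis also compares the observed event rate with the planning assumption to guide the length of follow-up. If the benchmark is too optimistic, a shortfall built into the arithmetic would be blamed on recruitment or on a low event rate.

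**Working it through.** **Inputs.** HR 0.75, 90% power, alpha 0.05, 515 events, rate 2.5% per year, 4,700 patients, five years, 10% discontinuation and 5,170 enrolled come from Sample size estimates; 1:1 allocation from Study design. Assumed: alpha is two-sided (this reproduces 515) and 2.5% is the no-aspirin rate (it is built from the earlier trial's patients not assigned to aspirin). The aspirin rate is then 0.75 x 2.5% = 1.875%.

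**1. Events.** Freedman: D = (1.75/0.25)² x (1.960 + 1.2816)² = 514.9, so 515. The plan's figure reproduces.

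**2. The 4,700.** With risk = 5 x rate: 12.5% and 9.375%, mean 10.94%. 515/0.109375 = 4,709, within 0.2% of 4,700. The plan's figure reproduces on linear risk.

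**3. The 5,170.** 4,700 x 1.10 = 5,170 exactly.

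**4. Inflation checked alone, on the plan's own linear risk.**
- 5,170 x 0.90 = 4,653, which is 47 below 4,700.
- 4,700/0.90 = 5,222.2, so 5,223 (53 more, 1.0%).
- 4,653 x 0.109375 = 509 events.
- Power = Φ(√D x 0.25/1.75 − 1.960); for D = 509 this is 89.7%.

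**5. Risk checked alone, constant hazard.**
- 1 − exp(−0.125) = 11.75%; 1 − exp(−0.09375) = 8.95%; mean 10.35%.
- 4,700 x 0.1035 = 486 events, power 88.3%.
- 515/0.1035 = 4,976 patients (5.9% above 4,700).
- If 2.5% is instead a yearly probability that compounds, 4,917 to 4,950 patients are needed.

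**6. Events from the 5,170 actually enrolled, constant hazard, five full years each.** For gradual loss, the loss rate is d = −ln(0.90)/5 = 0.0211 per year, and the event probability in an arm with hazard h is h/(h+d) x [1 − exp(−5(h+d))]: 11.17% and 8.50%, mean 9.83%.

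| Loss assumption | Expected events | Power | Years per patient to 515 |
|---|---|---|---|
| All 10% lost at once (4,653 x 0.1035) | 482 | 88.0% | 5.4 |
| 10% lost gradually over five years | 508 | 89.6% | 5.1 |
| Outcomes assessed in all (5,170 x 0.1035) | 535 | 91% | 4.8 |

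The 4.8 years: exp(−0.12) and exp(−0.09) give risks of 11.31% and 8.61%, mean 9.96%; 5,170 x 0.0996 = 515.

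**7. Calendar time.** The sample size section needs five years per patient, whereas Timing counts five years from the first patient with 18 months of enrolment. If accrual is uniform (assumed), mean potential follow-up is 5 − 0.75 = 4.25 years. At that date 5,170 patients give about 458 events with no loss and about 439 with gradual loss. Reaching 515 takes about 5.6 years from the first patient with no loss, 5.8 with gradual loss and 6.1 if the 10% are lost at once.

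**The case against.** The case on the other side has four parts.

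- **The linear step is consistent.** The plan turned 11.5% over four years into 2.88% per year by simple division. Multiplying back by years follows the same convention, and 4,700 then reproduces. A reader might infer that 4,700 contradicts the plan's assumptions. It does not: nowhere is 2.5% called a constant hazard. Treating the source figure as a hazard would also raise it, to −ln(0.885)/4 = 3.05%. And 2.5% was set by judgement above a derived 2.1–2.2%, a larger uncertainty than the choice of formula. This stands. It makes the step an approximation, though still one that overstates first events by about 6% (514 against 486 from 4,700 patients).
- **The 482 events are a worst case.** They require every discontinuer to contribute nothing. The analysis is by intention to treat in all randomised patients, visits continue after treatment is interrupted, and outcomes are to be assessed on withdrawal. This stands. A reader might infer that 5,170 cannot yield 515 events in five full years each; with complete outcome capture it yields about 535.
- **The inflation slip is 53 patients.** True, and it costs 0.3 points of power on linear risk. But it needs no modelling assumption to see, and it leaves the plan short of its own number.
- **The event-driven rule protects power.** A reader might infer that the trial lacks its 90%. At 515 events it has it, whatever the starting number. This stands, and it moves the consequence from power to duration.

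**Conclusion.** The point holds as a correction of stated figures. The discontinuation allowance is computed the wrong way: 5,170 leaves 4,653 after 10% loss, against 4,700 required. The 4,700 depends on a linear risk that, under a constant 2.5% control-arm rate, gives about 486 events in place of 515.

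For the enrolled 5,170 with five full years each, the expected count lies between 482 and 535 according to how discontinuers are followed, with power at that time between 88.0% and 91%. Final power at 515 events is not reduced, and the documents do not support calling the trial underpowered or requiring 5,529 enrolled (4,976/0.90), since that figure assumes loss at entry and ignores the event-driven rule.

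What is not supported is the forecast that five years from the first patient suffices when recruitment and event rate are on target. These results rest on two-sided alpha, 2.5% as the control rate, constant hazard and, for calendar time, uniform accrual. If 2.5% were the overall rate, 4,700 would be more than enough (4,383 with constant hazard), but the plan's 4,700 does not reproduce on that reading (4,120 with linear risk).

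**What to change.** Keep 5,170 enrolled and the 515-event target.

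1. In Sample size estimates, correct the allowance to n/(1 − 0.10), or state that 5,170 allows for about 9% loss (1 − 4,700/5,170 = 9.1%).
2. Say that 2.5% is the no-aspirin rate, name the formula that converts it to five-year risk, and give expected events at five full years per patient as about 482 to 535, naming the loss assumption behind each figure.
3. Restate the anticipated time to 515 events in Sample size estimates and Timing together, on one definition of follow-up that includes the 18 months of enrolment, in place of the statement that five years suffices.

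The cost is text only: no change to enrolment, endpoint or analysis, and a longer stated duration.
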